## 9.3 Recording of Adverse Events

During the AE reporting period stipulated in the protocol, the investigator is responsible for collecting all AEs (including SAEs) and recording them in the CRF/eCRF. When recording AEs, the investigator should use correct and standardized medical terminology to avoid colloquialisms and abbreviations. The start time of AE, the highest degree of NCI-CTCAE v5.0 grade, the end time, the correlation with the study drug, the impact on the study, the presence or absence of concomitant treatment and the recovery should be recorded.

**Diagnosis vs Symptoms and Signs**

If a diagnosis is already present, it should be recorded in the CRF/eCRF rather than individual signs and symptoms (e.g., record liver failure rather than jaundice, elevated transaminases, and throbbing tremor). However, if symptoms and signs cannot be classified as a single diagnosis at the time of reporting, each individual event should be recorded as an AE in the CRF/eCRF. If the diagnosis is later established, it should be updated on the CRF/eCRF to record the diagnosis.

**Adverse Events Secondary to Other Events**

In general, AEs secondary to other events (e.g., caused by other events or clinical sequelae) should have their primary event recorded, unless the secondary event is more severe or an SAE. However, secondary events with significant clinical significance should be recorded as independent AEs in the CRF/eCRF if they occur at a different time from the primary event; if the relationship between the events is unclear, the primary event and secondary event should be recorded separately.

**Continuous, intermittent or isolated adverse events (frequency of adverse events)**

Continuous AE refers to an AE persisting during the whole process without remission, for example, upper respiratory tract infection lasting for 5 days. Only one AE should be recorded in the CRF/eCRF. For severity assessment, the most severe severity throughout the event should be recorded.

Intermittent AEs are AEs that change or are relieved in symptoms, signs or laboratory parameters during the whole process, but do not have clinically significant outcomes, such as nausea and vomiting that last for many days, during which there is relative remission; subjects with hypertension have a relatively continuous course of hypertension despite intermittent remission in multiple blood pressure tests. Such AEs may be recorded in only one CRF/eCRF. The most severe severity over the course of the event should be recorded during the intensity assessment.

A separate AE (Single AE) is defined as an AE that can logically only occur alone, or that occurs only once independently in a trial, for example, an accident in which a

subject falls while on medication; and vomiting that a subject only experiences once during a trial. Only one such AE should be recorded on the CRF/eCRF.

It should be noted that if the above AE has been significantly clinically significant recovered, but the same AE occurs later and the latter is considered to have no continuous course with the former, the occurrence of the event should be recorded separately in the CRF/eCRF.

### **Laboratory abnormalities or vital signs**

All laboratory test results may be recorded on the laboratory results page of the CRF. Not all laboratory abnormalities/vital sign abnormalities should be recorded as AEs, and it is the responsibility of the investigator to review all laboratory abnormalities and abnormal vital signs and make medical judgment as to whether they should be recorded as AEs. Any of the above abnormalities with significant clinical significance, for example, one or more of the following conditions should be recorded as AE:

- Accompanying clinical symptoms
- Results in a change in study medication (e.g., dose modification, temporary or permanent discontinuation)
- Requires medical intervention or change in concomitant therapy (e.g., increase, suspension, discontinuation, or other change in concomitant medication, therapy, or treatment)
- Clinically significant as judged by the investigator

If a clinically significant laboratory abnormality or vital sign abnormality is a sign of a disease or syndrome (e.g., elevated ALT/AST and blood bilirubin due to hepatic impairment), only the diagnosis (i.e., hepatic impairment) should be recorded on the Adverse Event form of the CRF/eCRF. Otherwise, the laboratory test abnormality or vital sign abnormality should be recorded in the adverse event form of CRF/eCRF, indicating whether the test value is higher or lower than the normal range. If there are standard clinical terms corresponding to the laboratory abnormalities or vital sign abnormalities, the clinical term should be recorded in the CRF/eCRF

(e.g., "hyperkalemia" should be recorded when blood potassium increases to 7.0 mmol/L).

### **Death**

When recording a death event, if there is an AE leading to death, the AE leading to death should be recorded in the CRF/eCRF using a single medical concept and the event should be reported as an SAE; if the cause of death is unknown, "unexplained death" should be recorded in the AE form of the CRF/eCRF and reported as an SAE first, followed by further investigation into the exact cause of death, and the record and SAE report should be updated after the cause of death is known; if the death is due to tumor progression, it should not be recorded and reported as an AE/SAE.

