|--------------------------|------------------------------------------------------------------------------------------------------------------------------------------------------------------------------------------------------------------------------------------------------------------------------------------------------------------------------------------------------------------------------------------------------------------------------------------------------------------------------------------------------------------------------------------------------------------------------------------------------------------------------------------------------------------------------------------------------------------------------------------------------------------------------------------------------------------------------------------------------------------------------------------------------------------------------------------------------------------------------------------------------------------------------------|
|                          | 
Duration of response (DOR), overall survival (OS): Kaplan-Meier method was used to estimate DOR, OS and its 95% CI, and Kaplan-Meier curve was plotted.
 
Safety analysis
 
Including adverse events/adverse reactions, serious adverse events/serious adverse reactions, vital signs, laboratory tests, 12-Lead ECG, concomitant medication, etc. Based on SS, mainly descriptive statistics summary.
 
The number, percentage, and percentage of all adverse events, treatment-emergent adverse events (TEAEs), Grade 3 or higher TEAEs, Grade 3 or higher TEAEs related to study drug, treatment-emergent serious adverse events (SAEs), TEAEs related to study drug, SAEs related to study drug, TEAEs leading to treatment discontinuation, and TEAEs leading to death will be summarized by MedDRA dictionary by SOC and PT for each group.
 
Laboratory test results, vital signs, ECG and other data will be analyzed using conversion tables for baseline and post-baseline conditions.
 |

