### **2.5 Secondary Endpoints**

- Other efficacy indicators (based on RECIST 1.1 and iRECIST): 3-month ORR, PFS, DCR, DOR, OS;
- Incidence of adverse events: occurrence of all adverse events (AEs), serious adverse events (SAEs) and treatment-related adverse events (TEAEs);

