**Disease progression**

It should not be considered as AE if the occurrence of an event was clearly consistent with the expected pattern of progression of the primary tumor. Hospitalization solely due to progression of this disease is also not considered an SAE. If symptoms cannot be confirmed to be completely caused by disease progression, or it is inconsistent with the expected pattern of tumor progression, relevant clinical

symptoms may be recorded as AE, which conforms to SAE reportable SAE.

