## 9.6 Serious Adverse Events

### 9.6.1 Definition of Serious Adverse Events

An adverse event is classified as serious when the subject experiences an adverse event that meets one or more of the following criteria after receiving the investigational product: death, is life-threatening, results in persistent or significant disability or incapacity, requires or prolongs patient hospitalisation, is a congenital anomaly or birth defect, follows a pregnancy (spontaneous or induced abortion, termination of pregnancy for medical reasons), and is an important medical event (not immediately life-threatening or results in death, but may jeopardise the subject or may require intervention to prevent one of the other outcomes listed above).

Disease progression, including signs and symptoms of progression, should not be reported as a serious adverse event, but death due to disease progression should be reported as a serious adverse event if it occurs during the trial or safety reporting period. During the trial or safety reporting period, if the final outcome of cancer is death, the event that led to death must be reported as a serious adverse event.

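### Sections 9.3 and 9.6.1 give opposite instructions on whether a death from tumour progression is an SAE, so SAE incidence depends on which one is followed

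*Protocol*

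**What the plan says.** The Death paragraph of Protocol Section 9.3 covers three cases. A death caused by an AE is recorded under that AE and reported as an SAE. A death of unknown cause is first reported as an SAE and updated once the cause is known. For the third case, "if the death is due to tumor progression, it should not be recorded and reported as an AE/SAE".

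Section 9.6.1 starts from the position that progression, with its signs and symptoms, is not an SAE. It then makes an exception for death: "but death due to disease progression should be reported as a serious adverse event if it occurs during the trial or safety reporting period". Its next sentence repeats the point for the same period: "if the final outcome of cancer is death, the event that led to death must be reported as a serious adverse event".

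The Disease progression paragraph of Section 9.3 adds that "Hospitalization solely due to progression of this disease is also not considered an SAE". It does not mention death.

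Section 2.5 lists the incidence of AEs and SAEs as a secondary endpoint. The safety analysis in the Protocol Abstract says that "TEAEs leading to death will be summarized" by SOC and PT. The list of AE summaries in Section 11.3.5 includes SAEs but has no line for TEAEs leading to death.

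**The concern.** In advanced high-grade sarcoma, death from progression is an expected event, and the protocol classifies it in two opposite ways. Section 9.6.2 requires SAEs to be reported within 24 hours, so investigators apply the rule in real time from the protocol. One who withholds the report breaks 9.6.1, and one who sends it breaks 9.3.

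At stake is a descriptive secondary endpoint. If some progression deaths are reported as SAEs and others are not, the SAE incidence mixes two definitions. The same holds for fatal TEAEs, should that summary be produced. A later analysis plan can define how tables are built, but it cannot make the reporting consistent after the fact.

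**Working it through.** **Do the two instructions cover the same event in the same period?**

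| | Section 9.3, Death | Section 9.6.1 |
|---|---|---|
| Event | Death due to tumour progression | Death due to disease progression |
| Instruction | Neither record nor report as AE/SAE | Report as SAE |
| Period | The AE reporting period (opening of 9.3) | The trial or the safety reporting period |

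The events are the same and the periods overlap.

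**Can they be read together?** Three routes were tried.

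1. *9.3 governs the CRF and 9.6.1 governs SAE reporting.* This fails, because 9.3 rules out both recording and reporting.
2. *The Disease progression paragraph settles it.* It does not. It deals with progression events and with hospitalisation. On those it agrees with 9.6.1, and it is silent on death.
3. *One section takes precedence.* No section says so.

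The handling of unexplained deaths shows the conflict in practice. Such a death is first reported as an SAE. If the cause proves to be progression, 9.3 implies that the SAE is removed and 9.6.1 implies that it stays.

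**Size.** The protocol gives no figure to reproduce and no expected number of progression deaths in the reporting window. SAE incidence is counted per subject, so a progression death changes it only if the subject has no other SAE. The change per such death is then

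shift = 1/n

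The denominator n is the Safety Analysis Set (Section 11.1), taken here as equal to the planned enrolment in Sections 3 and 11.2.

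| n | Where it comes from | Shift per death |
|---|---|---|
| 10 | minimum of any cohort | 1/10 = 10.0 points |
| 30 | maximum of Cohorts 1 and 2; minimum total | 1/30 = 3.3 points |
| 40 | maximum of Cohort 3 | 1/40 = 2.5 points |
| 100 | maximum total | 1/100 = 1.0 point |

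With an assumed 1 to 5 such deaths in the whole trial, the shift runs from 1/30 = 3.3 to 5/30 = 16.7 points at a total of 30, and from 1 to 5 points at a total of 100. The fatal-TEAE rate moves by 1/n per progression death if the death is coded as a fatal TEAE.

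**The case against.** The strongest case on the other side is that little is lost. Survival follow-up (Section 6.2.6) runs to death and records its cause and date, so progression deaths can be identified under either rule. Drug-related SAEs and drug-related grade 3 or higher TEAEs are summarised separately, and a death due solely to progression would not ordinarily enter those tables. Deaths caused by an AE, and deaths still unexplained, are SAEs under 9.3 as well. There is no hypothesis test (Section 11.3.2). All of this stands. It limits the consequence but does not remove the contradiction.

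A reader might infer a much larger effect from the 49-week median OS and 18-week median PFS that Section 1.1 quotes for a soft tissue sarcoma cohort treated with pembrolizumab. With exponential survival, 18 weeks of treatment plus 30 days (22.3 weeks) gives 1 − 2^(−22.3/49) = 27% dead, and 104 weeks gives 1 − 2^(−104/49) = 77%. The documents do not support these as estimates for this trial:

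- They come from another drug, and two of the three cohorts here are alveolar soft part sarcoma, which is not among the subtypes listed for that study.
- They use a median PFS as everyone's treatment duration and count every death as a progression death.
- The 77% follows every subject for 24 months, although November 2021 to November 2023 is the whole trial including accrual. With the same median, uniform accrual over 12 months gives about 66% and over 24 months about 48%.

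A reader might also infer that results will differ between sites. The title says multicentre, but the Abstract names one study site. The conflict can produce inconsistency within one site as well as between sites, and divergence between sites is not shown.

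**Conclusion.** The contradiction is real and explicit in the current text. For a progression death in the AE reporting period, Sections 9.3 and 9.6.1 cannot both be obeyed. SAE incidence depends on the choice, as does the summary of TEAEs leading to death, which the Abstract plans and Section 11.3.5 does not list.

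The size is 1/n per progression death in a subject with no other SAE. One or two such deaths would be visible in a cohort of 10, while a single death would be minor in a total of 100. This assumes that the safety set equals planned enrolment; the number of such deaths is unknown.

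It would go too far to conclude that the safety results cannot be interpreted or that the drug-safety signal is swamped. ORR and OS are unaffected, the drug-related tables are essentially unaffected, and cause of death is collected. The point does not establish which reporting rule is right.

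**What to change.** Reconcile the Death paragraph of Section 9.3 with Section 9.6.1, so that both state the same single rule for deaths due to progression and the period to which it applies. Carry that rule through to SAE reporting, the eCRF and the safety tables, and bring any reports already made under the other instruction into line.

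Optionally, list deaths by cause from the data that Section 6.2.6 already collects, so that the SAE rate can be read with and without progression deaths. This is a convenience for the reader; reconciling the two sections is enough to correct the error.

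The cost is a change of wording in two sections, plus a check of existing reports. No new data are needed.

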### **Pre-existing medical conditions**

The preexisting symptoms/signs a subject has already presented during the screening period of the trial will be recorded as AEs only when there is worsening in severity, frequency, or nature (except for worsening of the medical condition under study) after entry into the trial. Changes from the previous state should be reflected in the records, such as "increased frequency of headache", "aggravated hypertension", etc.

### **Hospitalization, prolonged hospitalization**

The following situations result in hospitalization or prolonged hospitalization, which should not be reported as SAE:

Planned hospitalization or prolongation of hospitalization as required by the protocol (e.g., for dosing, efficacy assessment, etc.); Hospitalization for a medical condition that was present and unchanged prior to study participation, such as an elective procedure or treatment that was scheduled prior to study participation, the subject was hospitalized as scheduled for the procedure or treatment that occurred after study participation, is not considered an adverse event. However, if the condition of the existing disease worsens during the study (e.g., surgery or treatment should be performed earlier than originally planned), hospitalization for surgery or treatment is required due to the deterioration of the disease, and the deterioration of the condition

will be considered as an SAE.

**Surgery**

If the condition being treated by the procedure is known, the condition should be recorded as the AE rather than the procedure itself (e.g., if the subject has undergone inguinal hernia repair, an "inguinal hernia" should be recorded instead of "inguinal hernia repair"); however, if the reason for the procedure is unclear, the procedure may be recorded as the AE (e.g., if the subject has undergone abdominal exploration, an "abdominal exploration" may be recorded as the AE).

**Pregnancy**

If a female patient or a female partner of a male patient becomes pregnant during the clinical trial, the investigator should be notified immediately. The investigator should fill out the "Serious Adverse Event Report Form" within 24 hours after learning of the pregnancy event and report to the sponsor and the Ethics Committee, and follow up should continue until the outcome of pregnancy (such as termination of pregnancy, delivery), and report the results to the sponsor and the Ethics Committee. If a female patient becomes pregnant, study drug should be discontinued immediately and the investigator should discuss with the patient the risks of continuing the pregnancy and the possible effects on the fetus.

Artificial/spontaneous abortion, termination of pregnancy for medical reasons or fetus/newborn congenital abnormality or malformation during pregnancy should be considered as SAE, which should be recorded and reported according to the time limit for SAE.

**Disease progression**

It should not be considered as AE if the occurrence of an event was clearly consistent with the expected pattern of progression of the primary tumor. Hospitalization solely due to progression of this disease is also not considered an SAE. If symptoms cannot be confirmed to be completely caused by disease progression, or it is inconsistent with the expected pattern of tumor progression, relevant clinical

symptoms may be recorded as AE, which conforms to SAE reportable SAE.

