## **8. Efficacy evaluation**

TQB2858 injection is a tumor immune drug, and based on the experience of drugs in the same class, the subject may have false progression, i.e. The response assessment criteria for this study were based on RECIST 1.1, while iRECIST criteria were used to confirm response.

Beginning with Cycle 1 Day 1, efficacy will be assessed every 2 cycles over 1 year from the start of the study and every 4 cycles over 1 year until the subject experiences radiologically confirmed disease progression that does not change in frequency due to delay or interruption of treatment. If a subject discontinues study treatment for reasons other than disease progression, tumor imaging assessments at the aforementioned frequency should continue until the subject starts a new antineoplastic therapy, or radiographic evidence of disease progression, or the subject withdraws, or the subject dies, whichever occurs first.

CT or MRI can be used for tumor imaging evaluation at the discretion of the investigator, but the evaluation method, machine and technical parameters should be consistent throughout the study; if there is no contraindication, contrast agent should be used. If imaging has been performed within 28 months (within 3 months for bone scan) before the first dose, and the same method is used in the same center, it can be used as the baseline imaging index. Baseline Imaging examination CT or MRI of the neck, chest, abdomen, and pelvis should be included. Enhanced MRI (recommended) or enhanced CT is required at screening. Imaging should be performed at all suspicious lesion sites. For patients with bone metastasis, bone scan should be used for follow-up of lesions. For patients with bone metastasis, if there is no aggravation of clinical symptoms, each tumor assessment is not required for reexamination. If there is aggravation of clinical symptoms, reexamination should be performed in time. For patients with suspected disease progression before the next scheduled assessment,

unscheduled tumor assessment should be performed. During the trial, only the imaging examination of the lesion site is performed. If there is a suspicious site during the trial, the image of the corresponding site can be additionally examined.

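### Section 9.3 makes recording optional for symptoms not confirmed as progression, and no rule restores excluded events if the progression proves false

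*Protocol*

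**What the plan says.** Section 9.3 opens with a general duty: "the investigator is responsible for collecting all AEs (including SAEs") and for entering them in the CRF or eCRF. Section 9.1 defines an AE without requiring a causal link to the drug.

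The disease progression paragraph of Section 9.3 then sets two tiers.

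- **Clear cases.** For events, the rule reads: "It should not be considered as AE if the occurrence of an event was clearly consistent with the expected pattern of progression". A separate sentence deals with stays in hospital: "Hospitalization solely due to progression of this disease is also not considered an SAE".
- **Doubtful cases.** The trigger for this tier is worded: "If symptoms cannot be confirmed to be completely caused by disease progression, or it is inconsistent with the expected pattern of tumor progression". The instruction that then applies is that these "symptoms may be recorded as AE, which conforms to SAE reportable SAE".

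Section 9.6.1 has its own rule: "Disease progression, including signs and symptoms of progression, should not be reported as a serious adverse event". The same sentence goes on to require that death from progression be reported as an SAE during the trial or safety reporting period. The paragraph on death in Section 9.3 says that death from tumour progression is neither recorded nor reported as an AE or SAE.

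On false progression, Section 8 says of this drug class that "the subject may have false progression". Section 6.2.4 allows extra scans to confirm pseudoprogression, and Section 4.7 allows treatment to continue after progression if the investigator sees benefit.

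**The concern.** The doubtful tier is where a drug effect is most likely to be mistaken for disease. Read literally, a site that records nothing for such an event has followed the protocol. An event left out at this stage never reaches the causality assessment in Section 9.5, and no analysis plan can recover it, because analysis starts from what was recorded.

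False progression adds a second route. Symptoms or a hospital stay at an apparent progression may be set aside as disease. If later assessment does not confirm the progression, the protocol does not say that they must then be entered.

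Incidence of AEs and SAEs is a secondary endpoint (Section 2.5). The trial is open-label and single-arm, so no control group would reveal under-recording. The cohorts may be as small as 10 subjects (Section 11.2).

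**Working it through.** The protocol gives no AE rate, no rate of false progression and no share of doubtful events, so there is no figure to reproduce. The check sets the passages side by side.

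1. **General duty against the doubtful tier.** The opening of Section 9.3 covers all AEs, and the definition in Section 9.1 does not depend on cause. A symptom of uncertain origin is therefore an AE by definition, yet the disease progression paragraph says it *may* be recorded. The two instructions differ for the same event.

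2. **How Section 9.3 treats doubt elsewhere.** Symptoms that cannot yet be grouped under one diagnosis should each be recorded, and updated later. Events whose relation to each other is unclear should be recorded separately. An unexplained death should be recorded and reported first, then updated. In these paragraphs doubt leads to recording. In the disease progression paragraph it leads to discretion.

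3. **Link to causality.** Criterion 5 in Section 9.5 asks whether progression or another factor explains the event. In Table 7, the row for a possible relation has a plus on timing (criterion 1) and an uncertain entry on criterion 5. An event with plausible timing that cannot be confirmed as progression can fall in this row, and possible relation counts as an adverse reaction. If the event is not recorded, it drops out of both the AE incidence and the adverse reaction incidence.

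4. **Section 9.3 against Section 9.6.1.** Section 9.3 limits its exemptions to events "clearly consistent with the expected pattern of progression of the primary tumor" and to hospital stays due solely to progression. Section 9.6.1 exempts signs and symptoms of progression from SAE reporting with neither limit. The SAE rule is therefore broader than the AE rule on the same topic.

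5. **False progression.** Sections 8, 6.2.4 and 4.7 together foresee that it occurs, that it is checked on later scans, and that treatment may continue after progression. No passage says what happens to an event already excluded as progression. The update rule in Section 9.3 applies to symptoms already recorded; it does not create an entry for one left out.

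6. **Death from progression.** Section 9.3 says not to record or report it. Section 9.6.1 says to report it as an SAE. Both cannot be followed, and the choice changes the SAE count.

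7. **Scale per event.** One unrecorded SAE in a subject with no other SAE lowers the incidence by 1/n: 1/10 = 10 percentage points in the smallest cohort, 1/40 = 2.5 in the largest, and 1/30 = 3.3 to 1/100 = 1.0 for the whole trial. This is sensitivity per event. It does not estimate how many events would be missed.

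**The case against.** The strongest reply is that Section 9.3 is narrower than it may seem. A reader might infer that anything resembling progression is exempt, so that drug-caused symptoms and hospital stays are lost from the safety data. The text does not support that. The exemption needs an event to be clearly in line with the expected course, and a hospital stay to be due solely to progression; a stay caused by false progression meets neither on its face. The doubtful tier is itself a confirmation test, and symptoms at a first unconfirmed progression should fall into it. Excluding clear progression from AE recording is a legitimate choice.

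Other rules also work against loss: the general duty in Section 9.3, the instruction in Section 6.2.6 that AEs and SAEs must be reported, and the 24-hour SAE rule in Section 9.6.2. The document reads like a translation and uses *may* loosely elsewhere, for instance for laboratory results and intermittent AEs, so the word may not have been meant as permission.

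Much of this stands. It rules out the claim that events are lost, and it makes the false-progression route depend on an investigator treating an unconfirmed event as clear progression. It does not remove the core point. The tier meant to catch doubtful events is the one with permissive wording, the wording of Section 9.6.1 lacks the limits that make Section 9.3 defensible, and no passage restores an event once excluded. If *may* is a translation slip, sites still work from the text they have.

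**Conclusion.** The point holds as a risk of under-recording. Recording is optional for events not confirmed as progression, against the protocol's own general duty. Section 9.6.1 exempts more than Section 9.3, and there is no rule for events excluded under a progression that proves false. Such events may go unrecorded, and any bias in AE and SAE incidence would be downward.

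The size cannot be derived from the protocol. A reader might size it by multiplying an assumed rate of false progression by the sample size. That would count subjects with false progression, some of whom may have only a scan finding, and not events wrongly left out. The per-event figures above are the most that can be given.

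The conclusion assumes that sites read *may* as permission and that no separate instruction, such as the eCRF completion guide, already makes recording mandatory. The contradiction on death from progression needs neither assumption and changes the SAE count directly. Overall this is an inexpensive improvement worth making; it does not show that the safety data are unsound.

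**What to change.** Four edits to Sections 9.3 and 9.6.1.

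1. In the disease progression paragraph of Section 9.3, state that symptoms in the doubtful tier *must* be recorded as AEs, and reported as SAEs under Section 9.6.2 if a seriousness criterion is met.
2. In Section 9.6.1, limit the exemption for signs and symptoms of progression with the same two conditions as Section 9.3: clear consistency with the expected course, and hospital stays due solely to progression.
3. Add that if later assessment does not confirm the progression, the associated symptoms or hospital stay are entered as an AE or SAE from their original onset date.
4. Reconcile the paragraph on death in Section 9.3 with Section 9.6.1, so that death from progression is handled in one way throughout.

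Limiting the exemption to progression documented on imaging would not do the work of edit 3, because false progression also appears as progression on the first scan.

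The cost is a few sentences and a matching change to the eCRF completion guide, with no new visit or procedure. The downside is that some symptoms of true progression will be recorded, so AE counts rise slightly.
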